### Week 6 (end of treatment)

Uniocular assessment of visual acuity with a LogMAR test (aided with glasses if applicable) after sixth treatment.

### Week 10 (follow-up)

Full orthoptic assessment.

The independent assessor may perform additional tests such as the Sbisa bar and Frisby test if clinically indicated. The research orthoptist will record details of the treatment at each visit and ascertain whether the patient has had any adverse events.

At week 10 (follow-up), participation in the study will be complete for the patient and they will be returned to the care of the orthoptic department. Patients with residual amblyopia will receive standard treatment in line with departmental guidelines.

The patient may be withdrawn from the study at any point at the clinician’s discretion.

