### Design

The study is a randomised parallel group, double-masked design. Eligible patients are randomised to one of three treatments:

• I-BiT™ game

• Non-I-BiT™ game

• I-BiT™ DVD

They will receive their randomised treatment weekly for 6 weeks, for a 30-minute period (Figure 1). Their visual acuity will be assessed pre-treatment, after three treatments, after six treatments and 4 weeks after their final treatment. Visual acuity will be assessed by an independent assessor who has no knowledge of the randomised treatment. The orthoptist treating the patient will have no knowledge of the results of the patient’s visual acuity assessments. The study is therefore masked.

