### Randomisation and codebreaking

Subject numbers will be assigned sequentially as each subject enters the study. The subjects will be assigned to a study treatment arm through an independently-developed web-based randomisation system. Randomisation will be performed after eligibility has been checked prior to first treatment, and will be equal and stratified according to whether the patient has had previous treatment for their amblyopia. The research orthoptist will be the only member of the study team who will have knowledge of the randomised treatment.

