### Outcomes

#### Primary outcome

The primary variable is visual acuity. Visual acuity is measured in units of 0.025 (which equates to one letter). Improvement in visual acuity is measured as an increase of 0.025 LogMAR units.

The primary endpoint is the change from baseline to the end of treatment (6 weeks) in visual acuity.

The secondary endpoints are:

• Change in visual acuity from baseline to the end of the follow-up period (week 10)

• Change in visual acuity from baseline to week 3

• Proportion of patients showing a clinically important change in visual acuity (a change of 0.125 LogMAR units or more) at weeks 3, 6 and 10

• Proportion of change in visual acuity [9] at weeks 3, 6 and 10

• Change in binocular functions from baseline to week 6/week 10

• Proportion of patients reporting outcomes in each item of the patient satisfaction questionnaire

• Percentage compliance with treatment

• Proportion and type of adverse event

Proportion of change is measured as follows:

$$\mathrm{Proportion}\;\mathrm{of}\;\mathrm{change}=VA_{\mathrm{as}}-VA_{\mathrm{ae}}/VA_{\mathrm{as}}-VA_{\mathrm{fe}}$$

VA_as_ is vision of amblyopic eye at baseline, VA_ae_ is vision of amblyopic eye at the ‘end of treatment’ and VA_fe_ is the vision of the non-amblyopic eye at the’ end of treatment’ [9]. ‘End of treatment’ is the time point the change is being measured up to, that is, weeks 3, 6 and 10.

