### Safety assessment

All adverse events will be recorded. They will be categorised according to whether they are device related according to the Figure 2.

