## Discussion

This is the first randomised controlled study using the I-BiT™ system. It aims to determine whether the improvements in visual acuity observed in previous, uncontrolled studies of I-BiT™ technology are maintained under strict clinical trial conditions. It also aims to determine whether there is a difference between playing games and watching DVDs using I-BiT™ technology, and whether there is a difference between playing games using and not using the I-BiT™ technology and therefore identify which is the optimal treatment to develop.

Compliance is a huge issue with conventional patching treatment which impacts on the efficacy of the treatment. Therefore this study also aims to determine the compliance of patients undergoing each of the treatments.

The study also aims to determine whether there are any adverse effects which could be related to I-BiT™. It has been hypothesised that there is a theoretical risk of adverse events such as nausea, photosensitive epilepsy, headache, diplopia and reverse amblyopia. However, none of these events have been observed in previous studies.

It has not been possible to fully blind the study. However, the masking procedures ensure that clinical assessments are made in a blinded manner and therefore should not be subject to bias. The treating orthoptist will have no access to assessment results either through the database or through medical notes and indeed controls are in place to ensure that the treating orthoptist cannot treat these patients after they complete the study and thereby gain access to their resultant visual acuity measurement.

This study looks specifically at patients between the ages of 4 and 8 years. Cleary *et al.*[10] found improvements in older children in a pilot study with an I-BiT™ prototype system. Therefore it is possible that improvements could be gained in patients older than 8 years with the current I-BiT™ system. However, there are no plans formally assess this at present, the priority being to develop an optimal treatment regimen for children.

The results of this study will inform further development. It will be necessary to determine an optimal treatment regimen which may involve more frequent visits or a larger number of treatments in order to provide a long-term effect. It will also be necessary to follow-up patients in the longer term to ensure maintenance of beneficial effects.

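### Symptomatic adverse events are ascertained by the one team member who knows the allocation, so the Discussion's masking statement does not cover this secondary endpoint

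*Protocol article*

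**What the plan says.** Four parts of the protocol article bear on this.

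- **Knowledge of the arm** (Randomisation and codebreaking): "The research orthoptist will be the only member of the study team who will have knowledge of the randomised treatment".
- **Enquiry about events** (Week 10 (follow-up)): "The research orthoptist will record details of the treatment at each visit and ascertain whether the patient has had any adverse events".
- **Status of the data** (Outcomes): the secondary endpoints include "Proportion and type of adverse event". Under Safety assessment, all events are recorded and then sorted: "They will be categorised according to whether they are device related according to the Figure 2". That figure is not shown, and the text does not name who does the sorting.
- **Masking** (Design and Discussion): the Design section states "The study is a randomised parallel group, double-masked design" and explains the masking in terms of acuity: "Visual acuity will be assessed by an independent assessor who has no knowledge of the randomised treatment". It adds that the treating orthoptist does not see the acuity results. The Discussion concedes "It has not been possible to fully blind the study", and then says that "the masking procedures ensure that clinical assessments are made in a blinded manner and therefore should not be subject to bias".

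**The concern.** The article assigns two tasks to one role, and the two do not sit well together. The research orthoptist knows which treatment each child receives and is also the person who finds out whether the child has had an adverse event. Several of the anticipated events are symptoms. In a child of 4 to 8, whether a mild headache or a moment of double vision is recorded depends partly on how the question is put, how often, and what the questioner expects.

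What is at stake is the credibility of any comparison of adverse-event proportions between arms. The Discussion also makes it a study aim to find out whether any adverse effects could be related to I-BiT. Expectation about the active arms could inflate their counts, or confidence in the device could deflate them, and the data would not show which had happened. A reader who relies on the Discussion's general statement would not know that this endpoint falls outside the masking.

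**Working it through.** No effect size can be recomputed here, so the check is a comparison of the article's own statements.

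1. **Who is unmasked.** Randomisation and codebreaking names the research orthoptist, and nobody else on the study team.
2. **Who asks.** The Week 10 section names the research orthoptist again. Steps 1 and 2 use the same job title, so no inference is needed to link them.
3. **What the masking separates.** The Design section describes two barriers. The independent assessor does not know the arm, and the treating orthoptist does not know the acuity results. Neither barrier separates knowledge of the arm from the adverse-event enquiry.
4. **Which events are exposed.** Safety assessment lists five anticipated events: nausea, photosensitive epilepsy, headache, diplopia and reverse amblyopia. Three of the five (nausea, headache, diplopia) are symptoms that emerge mainly on questioning. Reverse amblyopia would show in uniocular acuity, which the masked assessor measures. If the treating and research orthoptist are the same role, as the article appears to mean, the orthoptist cannot see those results. The unmasked route therefore mainly concerns the symptoms.
5. **How far the Discussion's statement reaches.** It speaks of clinical assessments without restriction. Under Subsequent assessments, the visit assessments all belong to the independent assessor. For those examinations the statement fits. For adverse events, by steps 1 and 2, it does not.
6. **Primary endpoint.** Change in acuity to week 6 rests on the masked assessor's measurement, so steps 1 to 5 do not touch it. The planned size does not change either. The normal approximation with SD 0.25, difference 0.2, two-sided 5% and 80% power gives n = 2 × (1.960 + 0.842)² × 0.25² / 0.2² = 2 × 7.85 × 1.5625 ≈ 24.5. Rounded up, this is the stated 25 per arm (power 0.807). A t-test calculation gives 25.5 per arm, and power 0.791 at 25.
7. **Sensitivity of the safety endpoint.** If the endpoint is the proportion of children with an event, one child moves an arm's figure by 1/25 = 4 percentage points. This shows how coarse the endpoint is. It does not estimate bias: the article gives no event rates and nothing on differential reporting, so the bias has no calculable size.

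**The case against.** The strongest reply is that the article is open about this. It admits that full blinding was not possible, and it assigns adverse-event recording to the orthoptist in plain words. It uses the word assessment for the independent assessor's examinations, and the sentence after the masking statement is about acuity results. On that reading the Discussion is loosely worded rather than wrong. This largely stands. A reader might infer that the article conceals unmasked safety data behind a double-masked label, and the text does not support that. What remains is an unrestricted statement that should be restricted.

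A second reply concerns classification. A reader might infer that an unmasked person decides device-relatedness, and that events on the non-I-BiT game would then be called unrelated to the device as a matter of course, giving that arm a rate of zero. The documents support neither step. The classifier is not named, Figure 2 is not shown, a condensed article may leave this to the full protocol, and everyone on the team except the orthoptist is masked.

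A third reply is that the consequence is modest. Statistical methods calls secondary endpoints supportive, the article states no between-arm test of adverse events, Monitoring expects few events, and none of the anticipated events was seen in earlier studies. This stands as a limit on importance. It does not make the ascertainment masked.

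A fourth reply is that weekly enquiry by the treating orthoptist is a reasonable trade-off, and this also stands. It might seem that the masked acuity assessor should ask instead. But a child who mentions a DVD or a game at week 3 could unmask the assessor for the week 6 primary measurement, even if the questions follow that day's acuity test. Enquiry would also be less frequent.

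**Conclusion.** The point holds in a limited form. Symptomatic adverse events, and so the secondary endpoint built on them, are ascertained unmasked. The Discussion's statement is true of the independent assessor's examinations and should not be read as covering adverse events. The article fixes this by assigning both roles, so it is not a detail left to another document.

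The direction and size of any bias are unknown. A reader might infer from the 4-point step that a difference of several points between arms would be produced, but that would need an assumed number of differentially recorded events, and the documents supply none. The primary endpoint and the sample size are unaffected. The conclusion assumes only that the research orthoptist carries out the enquiry as described. It does not depend on who classifies device-relatedness.

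**What to change.** 1. **Standardise the enquiry.** Keep the research orthoptist asking at each visit, but from a fixed list of the anticipated symptoms (nausea, headache, diplopia) plus one open question, in identical words in all three arms. This limits variation in how the question is asked. It does not mask the questioner.
2. **Classify without allocation.** Have a study team member who is already masked judge device-relatedness from a listing that omits the arm and any free text that reveals a game or a DVD. Use one definition of the device for all three arms. This classification serves the endpoint and does not replace any safety reporting procedure.
3. **Correct the text.** Limit the Discussion's masking statement to the independent assessor's examinations, and say that adverse events are ascertained unmasked.
4. **Leave the acuity assessor out of symptom questioning**, to protect the week 6 measurement.

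The cost is a short form, a few minutes at visits that already take place, and somewhat more minor events, because they are now solicited. Trial status reports 21 of 75 children randomised at 6 November 2012. A form introduced then would cover the remaining 54 in full, and the report should say when the method of enquiry changed. Classification from a masked listing can be applied to all 75.

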**Figure 2 F2:**
[figure not shown]
Classification of adverse effects.

Events which could be considered to be anticipated due to the hypothesised mechanism of action of the treatment include nausea, photosensitive epilepsy, headache, diplopia and reverse amblyopia. None of these events have been observed in previous studies.

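### A loss of acuity in the good eye may not be counted as an adverse event, and it raises the proportion-of-change endpoint when the amblyopic eye has improved

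*Protocol article*

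**What the plan says.** All references are to the Protocol article.

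- **The harm.** The text under Figure 2, in the safety assessment part, lists the events anticipated from the mechanism of action: "nausea, photosensitive epilepsy, headache, diplopia and reverse amblyopia". The Discussion repeats the list as a "theoretical risk of adverse events such as nausea, photosensitive epilepsy, headache, diplopia and reverse amblyopia". Both places add that none has been seen in earlier studies.
- **Who ascertains adverse events.** Week 10 (follow-up): "The research orthoptist will record details of the treatment at each visit and ascertain whether the patient has had any adverse events".
- **Who knows the arm.** Randomisation and codebreaking: "The research orthoptist will be the only member of the study team who will have knowledge of the randomised treatment".
- **Who does not know the acuity.** Design: "The orthoptist treating the patient will have no knowledge of the results" of the acuity assessments. Discussion: "The treating orthoptist will have no access to assessment results either through the database or through medical notes".
- **Who measures acuity.** Under Subsequent assessments, an independent assessor performs all the assessments. Design says this assessor does not know the allocation.
- **Where good-eye acuity is used.** In the outcomes list it appears explicitly only in the proportion of change, where VA_fe "is the vision of the non-amblyopic eye at the" end of treatment, a term that the article then defines as weeks 3, 6 and 10.

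**The concern.** Reverse amblyopia shows as a fall in the acuity of the non-amblyopic eye. Nausea, headache or diplopia can be elicited by asking the child or parent. A modest acuity loss in one eye generally has to be measured. The person charged with asking about adverse events is kept from the measurements, and the person who measures is given no stated part in adverse-event reporting. If good-eye acuity is not reported in its own right, a final statement that no reverse amblyopia occurred would be weak evidence on a harm that the authors themselves anticipate. Safety is a stated secondary objective, and the Background presents the system as sparing the good eye.

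The second part concerns the direction of an efficacy measure. A denominator that contains the good eye's follow-up acuity shrinks when that eye gets worse, so a harm can appear as extra benefit. The two I-BiT arms favour the amblyopic eye, while the control game stimulates both eyes equally. Any mechanism-related loss could therefore fall unevenly across arms and tilt this endpoint towards I-BiT.

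**Working it through.** **Part 1: ascertainment, by setting the sections side by side**

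1. Week 10 (follow-up) gives ascertainment to the research orthoptist.
2. Randomisation and codebreaking makes that person the sole team member who knows the arm. Whoever delivers the treatment must know the arm, so the research orthoptist is evidently the treating orthoptist. No sentence says so; this is an inference.
3. Design and Discussion keep the treating orthoptist from acuity results, including through the database and the notes.
4. The independent assessor tests each eye separately at weeks 1, 3 and 6 and does a full orthoptic assessment at week 10. Good-eye values at weeks 3, 6 and 10 must exist, because VA_fe needs them.
5. No stated step carries a good-eye loss from the assessor to the adverse-event record. The acuity-based withdrawal rule at week 3 refers to the amblyopic eye only. No endpoint reports good-eye acuity alone, and Monitoring says that no data monitoring committee will be appointed.

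The data are therefore collected, but the stated rules do not ensure that a good-eye loss is counted as an event.

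**Part 2: the formula**

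The article gives no numerical result on this point to reproduce. Higher LogMAR is worse vision. The formula is printed without brackets; the evident reading is the ratio

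P = (VA_as − VA_ae) / (VA_as − VA_fe).

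The rate of change of P with VA_fe is (VA_as − VA_ae) / (VA_as − VA_fe)². Its sign is that of the amblyopic-eye gain: positive if that eye improved, zero if unchanged, negative if it worsened.

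Inputs: the acuities are assumptions, since the article gives none. The gain of 0.18 is the pilot mean in the Background.

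| Amblyopic eye | Good eye 0.00 | Good eye 0.10 | Good eye 0.20 |
|---|---|---|---|
| 0.50 to 0.40 (gain 0.10) | 0.10/0.50 = 0.20 | 0.10/0.40 = 0.25 | 0.10/0.30 = 0.33 |
| 0.60 to 0.42 (gain 0.18) | 0.18/0.60 = 0.30 | 0.18/0.50 = 0.36 | 0.18/0.40 = 0.45 |
| 0.50 to 0.32 (gain 0.18) | 0.18/0.50 = 0.36 | 0.18/0.40 = 0.45 | 0.18/0.30 = 0.60 |
| 0.40 to 0.22 (gain 0.18) | 0.18/0.40 = 0.45 | 0.18/0.30 = 0.60 | 0.18/0.20 = 0.90 |
| 0.50 to 0.50 (no change) | 0 | 0 | 0 |
| 0.50 to 0.55 (worse) | −0.05/0.50 = −0.10 | −0.05/0.40 = −0.125 | −0.05/0.30 = −0.167 |

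With baseline good-eye acuity (0.00 here) in the denominator, each row would keep its left-hand value whatever happened to the good eye.

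Two cautions:

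- **Brackets.** Taken literally as printed, the expression is VA_as − VA_ae/VA_as − VA_fe. For 0.50 to 0.40 this gives 0.5 − 0.8 − 0 = −0.3 with the good eye at 0.00, and −0.5 with it at 0.20. It falls as the good eye worsens, so the point rests on the ratio reading.
- **Gap between the eyes.** The assumed gaps of 0.4 to 0.6 fall short of the eligibility criterion as printed, a difference of at least 2 LogMAR units. With a gap of 2.0 the same 0.1 gain would move only from 0.1/2.0 = 5.0% to 0.1/1.8 = 5.6%. The direction holds, but the size depends on the gap.

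**The case against.** The strongest reply is that this is a condensed article. Reporting routes for adverse events are ordinarily set out in the full protocol, and by-arm safety tables and sensitivity analyses in the analysis plan, which the article says will follow. The article also commits to recording every adverse event, without limiting the source. The week 3 withdrawal rule turns on amblyopic-eye acuity, which the treating orthoptist cannot see, so somebody else must act on the assessor's results. On the formula, the definition is taken from a cited source, the endpoint is one of several supportive secondary ones, and the illustrative acuities are assumed.

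Much of this stands, and it rules out three stronger readings that a reader might infer:

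- **That the research orthoptist is the only person who can report an adverse event.** The article uses the word only for knowledge of the allocation, not for adverse-event reporting.
- **That good-eye losses will be missed, so that a null report is simply a product of the masking.** The masked assessor measures that eye, the values are in the data, and the full protocol may give a route.
- **That the index always rewards good-eye loss.** It does so only when the amblyopic eye has improved. A score of 100% (0.1/0.1) needs the good eye to fall from 0.0 to 0.4, an extreme that no figure in the article supports.

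The reply does not remove what the article does state: ascertainment assigned to a person denied the relevant measurement, and a follow-up value fixed in the denominator.

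**Conclusion.** The concern holds in a limited form. The stated roles leave a named, anticipated harm without a stated path into the adverse-event count, and no listed endpoint makes up for that. A null adverse-event report would say little about reverse amblyopia unless good-eye acuity is also shown. This rests on the inference that the research and treating orthoptist are the same person.

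On the ratio reading, good-eye loss inflates the proportion of change whenever the amblyopic eye has improved. In the assumed examples, a 0.2 LogMAR loss moves the score from 20% to 33% for a gain of 0.1. For the pilot mean gain of 0.18, it moves from 0.36 to 0.60 at an assumed baseline of 0.50. The direction is algebraic; the size depends on acuities that the article does not give. The effect is confined to one supportive secondary endpoint. The primary endpoint, the responder proportions and the sample size do not use the formula. The change is worth making because it strengthens the safety conclusion with data already collected.

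**What to change.** 1. **Safety outcome.** Report change from baseline in non-amblyopic-eye acuity by arm at weeks 3, 6 and 10, from the masked assessor's existing measurements. The article's own 0.125 LogMAR may serve as a descriptive cut-off for reporting, not as a clinical rule.
2. **Reporting route.** State that acuity-based adverse events are reported from the masked assessor's data, so that the Design, Week 10 (follow-up) and Discussion sections are reconciled. The assessor need not learn the arm, and the treating orthoptist need not see acuity results.
3. **Formula.** Print the brackets. Keep the cited definition if wished, and add a sensitivity analysis with the good eye's baseline acuity in the denominator.

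Cost: one extra table, one sensitivity analysis and a line on who reports acuity-based events. No new test or visit is needed and masking is preserved.

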
Previous pilot studies [5] have shown the I-BiT™ system to be highly effective in improving the visual acuity in amblyopic patients. Since we first began our studies, 3D technology has improved and we have recently conducted a pilot study to assess delivery of I-BiT™ treatment using the latest generation of shutter glasses technology [6]. This study showed that all patients who completed their planned treatment (9 of the 10 patients) showed an improvement in visual acuity. These improvements ranged from 0.025 to 0.45 LogMAR units with a mean of 0.18 (sd 0.143) and a median of 0.175.

While the study did have limitations (it was uncontrolled, unblinded and the sample size was small) the results were promising and warranted further investigation in a randomised controlled study. This study will aim to compare the effect of the I-BiT™ game with the I-BiT™ DVD and also to compare the effect of the I-BiT™ game with a control in which the patient plays the game without the amblyopic eye being preferentially stimulated.

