### Subsequent assessments

Patients will receive their randomised treatment for 30 min each week for 6 weeks. In addition to their baseline assessment, they will have assessments at the following visits, all performed by an independent assessor.

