### Week 3 (mid-treatment)

Uniocular assessment of visual acuity with a LogMAR test (aided with glasses if applicable) after third treatment.

If at this visit, visual acuity in the amblyopic eye has regressed by 0.1 LogMAR units or more, then the participants should be withdrawn from the study.

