### Statistical methods

The primary endpoint is considered confirmatory with secondary endpoints considered supportive.

The primary analyses will be performed on the intention-to-treat (ITT) population. Supportive analyses may be performed on a per protocol (PP) population defined prior to code-break.

Except where a patient has been withdrawn from the study or otherwise documented, all missing data will be assumed to be missing completely at random (MCAR). The primary analyses will not use any imputation methods to compensate for missing data.

There will be two primary comparisons: I-BiT™ games *vs.* non-I-BiT™ games and I-BiT™ DVD *vs.* I-BiT™ games. Both these analyses will comprise ANCOVA using baseline visual acuity as a co-variate, where distributional assumptions are met. If these assumptions are not met, a suitable transformation will be applied or a non-parametric method used. There will be no correction for multiplicity.

Summary statistics including mean, median, SD and 95% confidence intervals will be provided, in addition to appropriate graphical displays.

All datasets will be defined in a blinded manner prior to database lock.

Further details of the statistical analyses will be provided in the statistical analysis plan which will be finalised prior to database lock.

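### Withdrawing children from the study, rather than from treatment, when week-3 acuity worsens removes them from the week-6 ITT comparison on the basis of an early value of the outcome

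*Protocol article*

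**What the plan says.** In the protocol article, the section Week 3 (mid-treatment) sets a rule on the amblyopic eye: if at that visit "visual acuity in the amblyopic eye has regressed by 0.1 LogMAR units or more, then the participants should be withdrawn from the study". The section Week 10 (follow-up) adds a general clause: "The patient may be withdrawn from the study at any point at the clinician’s discretion". Neither limits the action to stopping treatment, and neither provides for acuity to be measured afterwards.

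Under Primary outcome: "The primary endpoint is the change from baseline to the end of treatment (6 weeks) in visual acuity". Under Statistical methods: "The primary analyses will be performed on the intention-to-treat (ITT) population", by ANCOVA with baseline acuity as the named covariate, and "The primary analyses will not use any imputation methods to compensate for missing data". The same section treats missing data as missing completely at random, with one exception: "Except where a patient has been withdrawn from the study or otherwise documented, all missing data will be assumed". It states no other handling of withdrawn children in the primary analysis.

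On the remaining visits, Subsequent assessments says of the children that "they will have assessments at the following visits, all performed by an independent assessor". Weeks 6 and 10 are among those visits.

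**The concern.** A site that follows the article as written takes a worsening child out of the study at week 3, three weeks before the primary endpoint. With no week-6 value and no imputation, that child contributes nothing to the primary ANCOVA, although the analysis is labelled ITT. The trigger is an earlier measurement of the primary variable itself, and the ANCOVA does not condition on it. The comparison is then between children in each arm who had not worsened by 0.1 LogMAR at week 3.

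If I-BiT works, more control than I-BiT children meet the rule. Removing them flatters the control arm, shrinks the estimated difference and costs power. The sample size is 25 per arm, and the article states no allowance for loss. The week-10 change and the responder proportions at weeks 6 and 10 lose the same children.

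The 0.1 LogMAR threshold as a reason to stop treating a child is not in question. The issue is that measurement stops as well.

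**Working it through.** **The plan's own figure.** Sample size section: SD 0.25, difference 0.2, two-sided 5%, 80% power. n per arm = 2 × (1.960 + 0.842)² × 0.25² / 0.2² = 2 × 7.85 × 1.5625 = 24.5, so 25. The stated figure reproduces (power 80.7% by normal approximation, 79.1% by t-test) and is not disputed.

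**Assumed inputs.** The article gives no week-3 SD, no week-3 to week-6 correlation and no control gain. Assumed:
- week-3 SD of change (s3) 0.10 to 0.143; the upper value borrows the pilot SD from Background ("with a mean of 0.18 (sd 0.143) and a median of 0.175"), which is not a week-3 figure
- correlation ρ between week-3 and week-6 change 0.3 to 0.7
- half of the week-6 gain present at week 3
- control gain 0 to 0.1, true difference 0.2, week-6 SD 0.25
- baseline SD 0.25, correlated 0.3 with both changes

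**Step 1: who is removed.** With improvement counted as positive, the proportion removed is Φ(a), where a = (−0.1 − week-3 mean) / s3.

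| s3 | control gain | control: a, removed | I-BiT: a, removed |
|---|---|---|---|
| 0.10 | 0.1 | −1.50, 6.7% | −2.50, 0.6% |
| 0.143 | 0.1 | −1.05, 14.7% | −1.75, 4.0% |
| 0.10 | 0 | −1.00, 15.9% | −2.00, 2.3% |
| 0.143 | 0 | −0.70, 24.2% | −1.40, 8.1% |

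**Step 2: shift in the difference.** Among those kept, the mean week-6 change rises by ρ × 0.25 × λ(a), with λ(a) = φ(a) / (1 − Φ(a)). Before baseline adjustment:
- mildest case (first row, ρ = 0.3): 0.3 × 0.25 × (0.139 − 0.018) = 0.009, so 0.20 becomes 0.191
- harshest case (last row, ρ = 0.7): 0.7 × 0.25 × (0.412 − 0.163) = 0.044, so 0.20 becomes 0.156

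**Step 3: the planned ANCOVA.** Simulation with 25 per arm, 40,000 trials per row. Full follow-up gives 0.200 and power 82%. Completers only:

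| s3 | control gain | estimate at ρ = 0.3, 0.5, 0.7 | power at ρ = 0.3, 0.5, 0.7 |
|---|---|---|---|
| 0.10 | 0.1 | 0.194, 0.188, 0.181 | 78.2%, 76.1%, 74.6% |
| 0.143 | 0.1 | 0.191, 0.181, 0.171 | 74.2%, 71.0%, 69.0% |
| 0.10 | 0 | 0.188, 0.176, 0.164 | 72.6%, 68.5%, 64.8% |
| 0.143 | 0 | 0.187, 0.174, 0.160 | 68.8%, 64.4%, 61.4% |

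A shorter independent rerun of the ρ = 0.3 and 0.7 cells agreed to within simulation error.

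**Step 4: where the effect is small, absent or reversed.**
- Pilot figures (difference 0.18, SD 0.143, control gain 0): estimate 0.159 to 0.173, power 97.1% to 98.4% against 99.5% with full follow-up.
- Identical arms: difference 0.00, type I error 4.9% to 5.2%.
- Equal means but a more variable I-BiT response (week-6 SD 0.25 v 0.143, week-3 SD 0.143 v 0.10): false difference 0.012 to 0.042 in favour of I-BiT, type I error 6.1% to 12.0%.
- No child meets the rule: no effect.

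**Step 5: children kept and measured.** If stopped I-BiT children revert to the control gain after week 3, the estimate is 0.192 to 0.199 and power 76.6% to 81.8%. If every stopped child also gains an assumed 0.1 LogMAR from standard care by week 6, the estimate is about 0.18 to 0.19 and power runs from the low seventies to about 80%. At ρ = 0.3 that estimate is no closer to 0.20 than completers-only, though power is higher.

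**The case against.** The strongest counter-argument is that an analysis can deal with the week-3 rule. The trigger is observed for every child the rule removes, so those values are missing at random given week-3 acuity. A likelihood analysis that also uses week-3 acuity, run on the same model, gave 0.199 to 0.204 against 0.199 to 0.203 with full follow-up. This stands, and a reader who infers that the loss is beyond repair goes too far. But the result requires that stopped children would have followed the same course as the others, it is not the primary analysis the article fixes, and it does not replace the lost measurements.

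A second argument is that handling may lie in documents not shown. The article exempts withdrawn children from the random-missingness assumption, refers further detail to the analysis plan, bars imputation only in the primary analyses, and lists LOCF among its abbreviations without using it. It does not expressly forbid a week-6 visit after withdrawal. That is fair, and it limits certainty about what sites did. It does not change the wording: withdrawal from a study ordinarily ends follow-up, and the article itself fixes both the withdrawal rule and the primary analysis without imputation.

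Two stronger readings are tempting and unsupported. One is that an unmasked clinician could steer withdrawals. The article does not say who the clinician is. The research orthoptist, who knows the treatment, is denied the acuity results. The effect of discretionary withdrawals cannot be derived. The other is that the rule manufactures a result in favour of I-BiT. When I-BiT works the bias is conservative. False positives rise only if responses differ in spread without differing in mean, and nothing in the article suggests that.

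**Conclusion.** The point holds for the week-3 rule. Followed as written, the plan drops children selected on an early value of the outcome from the comparison it labels ITT and confirmatory. The general discretionary clause shares the wording and is a secondary point without a number.

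Under the planning values and the assumed ranges, the estimate falls from 0.20 to about 0.16 to 0.19, and power from 82% to about 61% to 78%. The upper end of the loss needs week-3 SD 0.143, no gain in controls and correlation 0.7 together. With the pilot's figures the loss is under one letter (0.18 − 0.159 = 0.021, against 0.025 per letter) and power is hardly touched. These sizes are for the I-BiT game against the non-I-BiT game; the comparison with the DVD was not sized separately.

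This should be changed because the loss is avoidable and cheap to prevent. It does not invalidate the trial. Confidence is high on the structure and moderate on the size.

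**What to change.** Change both clauses from leaving the study to stopping treatment:
- Week 3: *If acuity in the amblyopic eye is worse by 0.1 LogMAR or more, study treatment is stopped.*
- Week 10, general clause: *Study treatment may be stopped at any time if the clinician judges it necessary.*
- Add to both: *The child stays in the study, completes the scheduled masked week-6 and week-10 acuity assessments unless consent is withdrawn, and is analysed as randomised. The reason for stopping and any standard care started are recorded.*

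An analysis that also uses week-3 acuity is a sensible sensitivity analysis, but not a substitute for keeping the children.

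Cost: a short amendment and no new assessments. Trial status gives 21 of 75 children randomised at the stated date, so it would cover at least the 75 − 21 = 54 still to enter. If the DVD arm behaves like the I-BiT game arm, the week-3 rule would stop about 25 × (0.067 + 0.006 + 0.006) = 2 to 25 × (0.242 + 0.081 + 0.081) = 10 children. They would attend up to two visits each that are already planned, 4 to 20 in all. Standard care begun after stopping may dilute the contrast, so retention reduces the power loss but may not restore the full 0.20.
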